## **6.2 Definitions of Analysis Sets**

Full Analysis Set (FAS): included patients who receive at least one cycle of neoadjuvant treatment.

Per-protocol Set (PPS): included patients who comply with the study protocol, have good compliance, do not take prohibited drugs during the treatment, receive surgery, and complete the CRF. Analysis of the efficacy should be performed in both FAS and PPS populations.

Safety Analysis Set (SAS): included patients who receive at least one cycle of neoadjuvant treatment and have safety records.

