#### **4.2 Neoadjuvant Treatment Period**

Intervention group: All enrolled patients receive 2-5 preoperative cycles of apatinib (500 mg orally once daily on days 1 to 21 and discontinued in the last cycle) plus SOX (S-1, 40-60 mg orally twice daily on days 1 to 14; oxaliplatin, 130 mg/m^2 intravenously on day 1) every 3 weeks.

- During neoadjuvant treatment, physical examination, ECOG PS assessment, tumor markers, and electrocardiograms are performed on day

1 of cycles 2, 3, 4, and 5. If cardiac pains or palpitations occur, myocardial enzyme spectrum (creatin kinase, lactate dehydrogenase), electrocardiogram, and cardiac ultrasound should be immediately performed;

- Peripheral blood routine and blood chemistry are performed on day 7 of cycle 1 and days 1, 7 of cycles 2, 3, 4, and 5;
- Urinary routine, stool routine, and coagulation tests are performed on day 1 of cycles 2, 3, 4, and 5;
- Imaging examination should be performed under the same conditions (layer thickness of scanning, use of contrast agent, etc.) as possible. The lesions detected at the baseline should be followed up every 2 cycles;
- Discomforts during the treatment should be recorded and graded according to the the NCI-CTCAE, version 4.0. If necessary, develop the treatment plan with the department of oncology, and record the reasons for dose adjustment or delay, supportive treatment, and outcomes in the CRF;
- Blood pressure monitoring is performed by the patient himself/herself and recorded in a diary card. Measurement should be done at least 3 times a week during the first 2 cycles. If abnormal, the blood pressure should be monitored daily; otherwise the blood pressure is measured weekly after 2 cycles. At each visit, researchers should measure the blood pressure again. Before measurement, smoking and coffee are not permitted. Take a sitting position. The elbows should be placed at the same level as the heart, and each measurement should be taken on the same side.

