#### **4.3 Preoperative evaluation and surgical period**

After completing neoadjuvant treatment, peripheral blood routine, blood biochemistry, stool routine, urine routine, 12-lead electrocardiograms, tumor markers, and coagulation function should be performed to evaluate the efficacy as well as the patients' physical condition. Without clear surgical contraindications and with the patients' consent, surgery will be performed 2–4 weeks later. If disease progresses, radiochemotherapy or salvage surgery is recommended.

- Record the results of peripheral blood routine, blood biochemistry, stool routine, urine routine, 12-lead electrocardiograms, tumor markers, and coagulation tests which are performed 7 days before and after the surgery;

- Retain pathological tissue specimens after surgery;
- Record the reasons for not surgery;
- Record operation time, blood loss, and intraoperative complications (e.g. major bleeding);
- Record postoperative complications and management;
- Record pathological type, number of lymph nodes harvested and metastasis;
- Record postoperative hospital days.

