#### 4.4 Adjuvant treatment period

Intervention group: All enrolled patients receive 6 postoperative cycles of apatinib (500 mg orally once daily on days 1 to 21) plus SOX (S-1, 40-60 mg orally twice daily on days 1 to 14; oxaliplatin, 130 mg/m^2 intravenously on day 1) every 3 weeks.

- During adjuvant treatment, peripheral blood routine and blood chemistry are performed on days 1, 7 of cycle 1 and day 1 of cycles 2, 3, 4, 5, and 6;
- Physical examination, ECOG PS assessment, tumor markers, and electrocardiograms are performed on day 1 of each cycle;
- Imaging examination should be performed under the same conditions (layer thickness of scanning, use of contrast agent, etc.) every 3 cycles;
- Discomforts during the treatment should be recorded and graded according to the NCI-CTCAE, version 4.0. If necessary, develop the treatment plan with the department of oncology, and record the reasons for dose adjustment or delay, supportive treatment, and outcomes in the CRF;
- Blood pressure monitoring is performed by the patient himself/herself and recorded in the diary card. Measurement should be done at least 3 times a week during the first 2 cycles. If abnormal, the blood pressure should be monitored daily; otherwise the blood pressure is measured weekly after 2 cycles. At each visit, researchers will measure the blood pressure again. Before measurement, smoking and coffee are not permitted. Take a sitting position. The elbows should be placed at the same level as the heart, and each measurement should be taken on the same side.

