#### **- Secondary Efficacy Measures**

Calculate the pathological/radiologic response rate with 95% CI. The Kaplan-Meier method is used to analyze overall survival (OS) and disease-free survival (DSS), and the differences are assessed with log-rank tests.

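### OS and DFS are sent into a per-protocol set defined by later surgery and compliance, with no stated time origin, so the PPS survival curves run high

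*Protocol*

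**What the plan says.** Section 6.2 (Definitions of Analysis Sets) defines two efficacy sets. The FAS "included patients who receive at least one cycle of neoadjuvant treatment". The PPS is defined as follows: "included patients who comply with the study protocol, have good compliance, do not take prohibited drugs during the treatment, receive surgery, and complete the CRF". The rule for using them is general: "Analysis of the efficacy should be performed in both FAS and PPS populations".

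Under Efficacy, Secondary Efficacy Measures, the protocol states: "The Kaplan-Meier method is used to analyze overall survival (OS) and disease-free survival (DSS" (the abbreviation there is evidently a slip for DFS). The synopsis also lists DFS and OS as secondary outcomes.

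No section gives a time origin for either endpoint. The only clock is in section 3.4, where follow-up of each participant begins on the date of consent. That is a follow-up start, not an endpoint definition.

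The timetable before surgery is fixed in two places. Section 4.2 says "All enrolled patients receive 2-5 preoperative cycles of apatinib", in three-week cycles, and section 4.3 says that "surgery will be performed 2–4 weeks later", counted from the end of neoadjuvant treatment.

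**The concern.** PPS membership is decided by what happens after treatment starts. A patient who dies before the operation cannot enter the PPS, so nobody in it can die in that window. If the survival clock is already running, the window counts as time at risk although no death is possible in it. This is immortal-time bias, and it raises the curve.

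A second mechanism does not depend on the clock. Patients with poor prognosis tend to leave the PPS:

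- For disease progression, section 4.3 points to radiochemotherapy or salvage surgery, while section 3.2.3 makes radiation during the study a ground for rejection.
- Appendix 5 withdraws patients with perforation, serious bleeding and similar events.

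The trial has one arm, so no concurrent control carries the same bias, and a reader will compare the curves with other series. The problem is also separate from the denominator of the R0 rate: reporting R0 in the FAS would not cure it.

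**Working it through.** The protocol gives no survival rate, event count or power, so there is no figure of its own to reproduce. All survival rates below are assumptions, shown as ranges.

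**Guaranteed time to surgery, from treatment start.** Inputs: 2 to 5 cycles of 3 weeks (section 4.2) and 2 to 4 weeks to surgery (section 4.3), counted here from the end of the last three-week cycle.

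- Shortest: 2 × 3 + 2 = 8 weeks = 1.84 months
- Longest: 5 × 3 + 4 = 19 weeks = 4.37 months
- FAS, if its one cycle must be completed: 3 weeks = 0.69 months

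(Months are weeks divided by 52.1775/12.) A clock started at consent adds the time between consent and first dose.

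**Effect of the guarantee alone.** With guaranteed time L, S_PPS(t) = S(t)/S(L). Under an assumed constant hazard with median m, S(t) = 0.5^(t/m). At t = 36 months:

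| Assumed median OS | S(36), all patients | PPS, L = 8 weeks | PPS, L = 19 weeks | Excess (points) |
|---|---|---|---|---|
| 24 months | 35.4% | 37.3% | 40.1% | 1.9 to 4.8 |
| 36 months | 50.0% | 51.8% | 54.4% | 1.8 to 4.4 |
| 60 months | 66.0% | 67.4% | 69.4% | 1.4 to 3.4 |

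For the middle row: 0.500 / 0.5^(1.84/36) = 0.518 and 0.500 / 0.5^(4.37/36) = 0.544.

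**Against the FAS.** At a 36-month median the FAS itself shows 0.500 / 0.5^(0.69/36) = 50.7%. The PPS excess over the FAS is then 51.8 − 50.7 = 1.1 to 54.4 − 50.7 = 3.7 points.

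**Deaths that the model implies before surgery.** For L = 19 weeks, 1 − 0.5^(4.37/60) = 4.9% and 1 − 0.5^(4.37/24) = 11.9%, or roughly 2 to 6 of 50 patients. Fewer early deaths would shrink the excess nearly in proportion.

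**Selection.** This was simulated with 1,000,000 patients, assuming that 10-20% never reach the PPS and have 2 to 3 times the hazard of the others.

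| Clock starts at | PPS when all patients are at 50% | PPS when all patients are at 70% |
|---|---|---|
| Treatment start (guarantee plus selection) | about 54-62% | about 73-79% |
| Surgery (selection only) | about 52-58% | about 72-76% |

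Without selection, starting the clock at surgery removes the excess: 50.0% stays 50.0% and 70.0% stays 70.0%.

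**Scale.** The 95% CI half-width for a proportion at n = 50 is 1.96 × √(0.5 × 0.5/50) = 13.9 points at 50%, and 12.7 points at 70%.

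**The case against.** **The efficacy rule may not cover survival.** Sections 2.2 and 3.5.1 list the secondary efficacy endpoints without OS and DFS. On that list, the two-set rule would reach only R0 and the response rates. This shows loose drafting but does not undo the instruction: the analysis section places OS and DFS under Secondary Efficacy Measures, and the synopsis lists both as outcomes.

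**The time origin is unstated and may be left to an SAP.** This stands in part. The missing origin alone would be no finding. A reader might infer that guaranteed months certainly count as time at risk; the protocol does not establish that. If DFS is counted from resection, the presurgical window does not enter it. What the protocol does fix is the pairing of survival with the PPS, and selection then remains under any origin.

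**The adjuvant phase.** A reader might extend the guaranteed time through adjuvant treatment, because section 4.4 says "All enrolled patients receive 6 postoperative cycles of apatinib". Six three-week cycles add 18 weeks, giving 26 to 37 weeks (recovery time taken as zero) and an excess of 4.7 to 9.8 points on the same model. The text does not support this. The PPS definition names surgery as its only treatment milestone and does not equate compliance with finishing six cycles. Section 3.2.4 lists progression and death as reasons to stop treatment, so a patient who stops for either has followed the protocol.

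**Little is hidden.** The FAS curve is also required, the primary endpoint is R0, and no decision rule rests on PPS survival. The excess from the guarantee is small beside a half-width of 13 to 14 points. All of this is true and limits the weight of the point. However, the interval measures random error and does not cover a systematic shift, and the protocol does not say which set leads for survival.

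**Conclusion.** The point holds in limited form. As written, the protocol calls for OS and DFS in a set conditioned on events after baseline, with no stated origin. With a clock started at treatment start, and a little more so from consent, PPS members carry 8 to 19 weeks of guaranteed survival. That puts 3-year OS about 1.4 to 4.8 points too high, and slightly less relative to the FAS. These figures rest on a constant hazard and a median OS of 24 to 60 months, neither of which the protocol gives. With a clock started at surgery this part is zero. Selection stays upward under either origin, and its size depends on how many patients miss the PPS and how much worse they do.

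A reader might conclude that all the survival results are biased. The documents do not support that: the required FAS analysis is largely free of the problem, and the R0 endpoint is untouched by it.

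**What to change.** In section 6.2:

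1. Limit the PPS analysis to R0, pathological and radiologic response.
2. Estimate OS in the FAS from a stated origin, either consent or first dose.
3. Estimate DFS from the date of resection in all FAS patients who were resected disease-free, without selecting on later compliance, and describe it as applying to those patients.
4. Report any survival of operated patients only as a supplementary landmark analysis from surgery, labelled as describing a selected group. The landmark removes the guaranteed time but not the selection.

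The cost is a few sentences and the loss of the PPS survival curve. No additional patients, visits or data are needed.

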### 3.3.2 Drug Administration

- Oxaliplatin, 130 mg/m^2 intravenously on day 1;
- Apatinib, 500 mg orally once daily on days 1 to 21;
- S-1 (Tigio), 40-60 mg orally twice daily on days 1 to 14.

The dose of S-1 is based on body surface area (BSE):

| BSE                                    | Dose     |
|----------------------------------------|----------|
| < 1.25m                    | 40mg Bid |
| 1.25m  - 1.5m  | 50mg Bid |
| > 1.5m                     | 60mg Bid |

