## **6.2 Statistical Analysis**

Baseline data are described as mean with standard deviation (SD), median, and range in case of continuous variables and as frequencies with percentages in case of categorical variables.

All statistical analyses will be conducted with SPSS software, version 22.0 (SPSS Inc., Chicago, IL, USA). A two-tailed P value less than 0.05 is considered to be statistically significant.

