### **● Efficacy**

#### **- Primary Efficacy Measures**

Calculate the R0 resection rate with 95% confidence interval (CI).

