#### 3.2 Principles for Dose Adjustment and Interruption

- Dose reductions are allowed in the presence of grade 3 treatment-related toxicities.
- Among non-hematological toxicities, there is no need to reduce the dose or discontinue the treatment in the presence of manageable nausea, vomiting, hair loss, fever with a defined cause (such as infection or tumor), and grade 3/4 elevated alkaline phosphatase (AKP).
- Dose reductions are allowed up to twice. Treatment interruption is allowed for no more than 14 days (cumulatively) and no more than two times in each cycle. Dose re-escalation is not permitted.
- Treatment interruption is first performed during each cycle. Then dose reduction can be performed when the subject is still intolerant.
- Special AEs: Once hypertension crisis, cerebral hemorrhage, grade 2 or higher pulmonary hemorrhage, grade 3 or higher other bleeding, arterial thrombosis, grade 4 venous thrombosis, leukoencephalopathy syndrome, or gastrointestinal perforation occurs, immediately discontinue the treatment and perform active symptomatic treatment; the subject then withdraw from the study.

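### Both the full analysis set and the safety set start at one cycle of treatment, so on the plain reading patients who stop for good during cycle 1 leave the R0 denominator and the safety-set toxicity rates

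*Protocol*

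**What the plan says.** Section 6.2 (Definitions of Analysis Sets) gives the efficacy set as "Full Analysis Set (FAS): included patients who receive at least one cycle of neoadjuvant treatment". The safety set uses the same threshold with one further condition: it "included patients who receive at least one cycle of neoadjuvant treatment and have safety records". The same section adds: "Analysis of the efficacy should be performed in both FAS and PPS populations". The per-protocol set is narrower still, because it requires surgery. No set counts everyone enrolled or everyone who took a first dose.

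Section 3.3.2 sets the content of a cycle: oxaliplatin on day 1, S-1 on days 1 to 14, and "Apatinib, 500 mg orally once daily on days 1 to 21". Section 4.2 repeats cycles every 3 weeks: "All enrolled patients receive 2-5 preoperative cycles of apatinib".

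Treatment can end for good inside cycle 1. Section 3.2.4 lists progression, intolerable toxicity, refusal, investigator decision and death. Appendix 5 (item 3.2, on apatinib) lists special events, including bleeding of grade 3 or above, arterial thrombosis and gastrointestinal perforation. For these the instruction is to "immediately discontinue the treatment and perform active symptomatic treatment; the subject then withdraw from the study".

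Section 3.2.3 and the synopsis also give rejection criteria. Two of them are incomplete data and departure from the prescribed medication. The protocol does not say how these relate to the analysis sets.

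**The concern.** A patient who takes the first doses, perforates on day 10 and is withdrawn has been exposed to the regimen and has failed on it. If membership requires a cycle to have been received, that patient counts neither as an R0 failure nor as a toxicity case. The rule then selects on what happened after treatment began, and the patients it removes are those who did worst earliest.

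The study is single-arm (section 3.1). Its R0 rate and toxicity rates are the result, and no comparison group carries the same exclusion. Both errors run in the regimen's favour: the R0 rate goes up and the rates of early severe toxicity go down.

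**Working it through.** **Inputs from the protocol.** N = 50 (synopsis), single arm. The set definitions, cycle content and stopping rules are those cited above. The protocol states no target R0 rate, precision or cycle 1 loss rate, so there is no figure of its own to reproduce. The 50 serves only as the number starting treatment.

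**Assumptions.** All 50 take at least one dose. k patients stop for good in cycle 1, with k from 1 to 5, and none of them is resected R0. R patients in total are resected R0, with R = 35, 40 or 45.

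**R0 rate.** The rate among all dosed is R/50. The rate under the one-cycle threshold is R/(50 − k). The inflation is R/(50 − k) − R/50 = R·k / [50(50 − k)].

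| k | R = 35 | R = 40 | R = 45 |
|---|---|---|---|
| 0 | 35/50 = 70.0% | 40/50 = 80.0% | 45/50 = 90.0% |
| 1 | 35/49 = 71.4% (+1.4) | 40/49 = 81.6% (+1.6) | 45/49 = 91.8% (+1.8) |
| 2 | 35/48 = 72.9% (+2.9) | 40/48 = 83.3% (+3.3) | 45/48 = 93.8% (+3.8) |
| 3 | 35/47 = 74.5% (+4.5) | 40/47 = 85.1% (+5.1) | 45/47 = 95.7% (+5.7) |
| 5 | 35/45 = 77.8% (+7.8) | 40/45 = 88.9% (+8.9) | 45/45 = 100% (+10.0) |

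Exact (Clopper-Pearson) 95% intervals move in the same way. 40/50 gives 66.3 to 90.0%, and 40/47 gives 71.7 to 93.8%.

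**Toxicity, event confined to the lost patients.** The rate among all dosed is k/50. The rate in the safety set is 0/(50 − k).

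| k | All dosed (exact 95% CI) | Safety set (exact 95% CI) |
|---|---|---|
| 1 | 2.0% (0.1–10.6) | 0/49 (0–7.3) |
| 2 | 4.0% (0.5–13.7) | 0/48 (0–7.4) |
| 3 | 6.0% (1.3–16.5) | 0/47 (0–7.5) |
| 5 | 10.0% (3.3–21.8) | 0/45 (0–7.9) |

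**Toxicity, event also seen later.** If T of 50 have the event and one of them is lost, T/50 becomes (T − 1)/49. With T = 10, 20.0% becomes 9/49 = 18.4%, a drop of 1.6 points. With T = 25, 50.0% becomes 24/49 = 49.0%, a drop of 1.0 point.

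**How likely is at least one such patient?** The probability is 1 − (1 − p)^50, where p is the assumed chance per patient of being lost in cycle 1. It is 64% for p = 2%, 87% for 4%, 95% for 6% and 99% for 10%.

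**The case against.** The definitions speak of receiving a cycle, not completing one. The protocol never says that 21 days of apatinib make a cycle. Section 4.2 counts the last preoperative cycle as a cycle although apatinib is left out of it, and oxaliplatin is given on day 1 only. The sponsor may mean that cycle 1 was started. This stands as an ambiguity. Receiving a whole cycle is still the natural reading, and the set behind the primary endpoint should not depend on a guess.

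A reader might infer that cycle 1 events vanish from the safety results altogether. The protocol does not support that. Section 5.1 monitors adverse events from trial entry, section 5.3 requires serious events to be recorded and reported within 24 hours, and the safety paragraph of section 6.2 asks for a listing of every adverse event without naming a set. What can be lost is the place of these events in safety-set rates.

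Four other strong readings also fail:
- It is not a general rule that each lost patient removes 2 points of toxicity. That is roughly so only when the event is absent among those who stay, as the calculation with later events shows.
- The safety-records condition is not shown to select on outcome. With monitoring from entry, a patient with an early haemorrhage would have a record. The condition is redundant rather than harmful.
- Progression is a weak route out of cycle 1. Imaging is every 2 cycles, so only clinical progression or an unscheduled scan would count.
- Death is not among the special events in Appendix 5. It ends treatment under section 3.2.4.

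Finally, the primary analysis is a rate with a 95% interval, and the protocol states no null or target rate. The inflation therefore crosses no stated decision threshold. This bears on how serious the point is, not on the direction of the bias.

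**Conclusion.** The point holds for the rates and denominators. On the plain reading of section 6.2, patients who stop for good during cycle 1 are left out of both the full analysis set and the safety set, and no other set recovers them. The defect lies in a rule that the protocol itself fixes, not in detail left to a statistical analysis plan.

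The bias favours the regimen. It inflates the R0 rate by about 1.4 points (k = 1, R = 35) to 10.0 points (k = 5, R = 45). An event confined to the lost patients is reported as 0% instead of 2% to 10%, and the understatement is smaller if the event also occurs later. These sizes rest on assumed values of k and R, and on no lost patient being resected R0 afterwards. If some were, the inflation would be smaller. If the sponsor means that cycle 1 was started, there is no such bias, but the wording still has to say so.

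**What to change.** Change section 6.2 (Definitions of Analysis Sets) as follows:

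- **Safety set:** all patients who took at least one dose of any study drug. Delete the safety-records condition.
- **Full analysis set:** all enrolled eligible patients who took at least one dose of any study drug, whether or not cycle 1 was completed. Count every patient without an R0 resection as not R0, including those never operated on.
- **Rejection criteria (synopsis and section 3.2.3):** state that incomplete data and departure from the prescribed medication do not remove a patient from either set. Without this sentence, early stoppers could still be dropped after the definitions are corrected.

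The per-protocol set can stay as a supporting analysis. No treatment rule or data collection changes. The cost is a few sentences, with an R0 rate that may be slightly lower and toxicity rates that may be slightly higher than under the present wording.
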